### Concurrent Medications

**Details of all con-meds will be recorded in the CRF.**

# STUDY ASSESSMENTS

## STUDY VISITS

(***See Appendix 2 ALTERED Participant study schedule)***

As outlined in section 5.2, participants will be provided with a full PIS and are given at least 24 hours to consider their response before a screening visit will be arranged for consent to be taken and to check their eligibility by all the criteria.

**Phase 1 Dose Escalation Study**

- **Visit 1 –Screening visit 1**
  - Participant consent– answer any outstanding questions and complete consent form.
  - Clinical Examination, Medical and Family history
  - Baseline Urate bloods
  - Safety bloods
  - Record list of current medications
- **Visit 2 Randomisation visit (Day 0) upto 4 week post screening**
  - Dosing with Allopurinol
  - Supply of 1^st^ dose study medication allopurinol 100mg x 3 dialysis sessions 7 days (+/- 1 dialysis session)
  - Record list of current medications
  - Vital signs
  - Assess any adverse events from screening visit to randomisation
  - Safety bloods
- **Visit 3- Progress visit at 4^th^ Dialysis Session**
  - Review urate and safety bloods
  - If urate decreased by >50%- **no further visits**
  - If urate decreased by <50%- titrate up to 200mg allopurinol
  - Stat Dose 200mg Allopurinol
  - Supply of 2nd dose study medication allopurinol 200mg x 3 dialysis sessions (+/- 1 dialysis session)
  - Record list of current medications
  - Vital signs
  - Assess any adverse events from visit 2 to visit 3
  - Check drug compliance
- **Visit 4- Progress visit at 7^th^ Dialysis Session**
  - Review urate and safety bloods
  - If urate decreased by >50% from screening - **no further visits**
  - If urate decreased by <50%- titrate up to 250mg allopurinol
  - Stat Dose 250mg Allopurinol
  - Supply of 3rd dose study medication allopurinol 250mg x 3 dialysis sessions (+/- 1 dialysis session)
  - Record list of current medications
  - Vital signs
  - Assess any adverse events from visit 3 to visit 4
  - Check drug compliance
- **Visit 5- Progress visit at 10^th^ Dialysis Session**
  - Review urate and safety bloods
  - If urate decreased by >50% from screening - **no further visits**
  - If urate decreased by <50%- titrate up to 300mg allopurinol
  - Stat Dose 300mg Allopurinol
  - Supply of 4th dose study medication allopurinol 300mg x 3 dialysis sessions (+/- 1 dialysis session)
  - Record list of current medications
  - Vital signs
  - Assess any adverse events from visit 4 to visit 5
  - Check drug compliance
- **Visit 6- Progress visit at 13^th^ Dialysis Session**
  - Review urate and safety bloods
  - If urate decreased by >50% from screening - **no further visits**
  - If urate decreased by <50%- titrate up to 350mg allopurinol
  - Stat Dose 350mg Allopurinol
  - Supply of 5th dose study medication allopurinol 300mg x 3 dialysis sessions (+/- 1 dialysis session)
  - Record list of current medications
  - Vital signs
  - Assess any adverse events from visit 5 to visit 6
  - Check drug compliance
- **Visit 7- Final visit at 16^th^ Dialysis Session (+/- 1 dialysis session)**
  - Review urate and safety bloods
  - Record list of current medications
  - Vital signs
  - Assess any adverse events from visit 4 to visit 5
  - Check drug compliance

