**Phase 1 Dose Escalation Study**

A preliminary study will be undertaken to see which dose of active allopurinol reduces plasma urate by the same margin (41%) as seen in our CKD stage 3 study where allopurinol did regress LVH.[[21](#_ENREF_21)]

Ten patients with end stage renal disease (CKD stage 5) who have been on haemodialysis for at least 3 months will initially receive open label 100mg allopurinol **after each** dialysis session for 3 sessions. Plasma urate will be checked at the commencement of the fourth dialysis session. Thereafter the allopurinol dose will be increased to 200mg and the same procedure repeated. The next step will be 250mg and then 300mg and 350mg (maximum dose). The dose escalation will stop in each patient when plasma urate has fallen by 50% in that patient which is in keeping with published recommendations to ensure safe prescribing of allopurinol in ESRD. [[28](#_ENREF_28)] From these pilot data, we will calculate which of the above doses of allopurinol (given at the end of each dialysis session) produces on average a 41% fall in plasma urate. This will be the chosen dose for the main trial.

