**Treatment Allocation**

Open Label Phase 1 Study (n=10 completed)

if >50% decrease from baseline in urate level **stop** in trial or continue until 350mg allopurinol max dose

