**N*ote visits 3a- 3d are dependent on pilot data deciding eventual optimum dose of allopurinol***

**Visit 3a- Progress visit (Week 2 +/- 1 dialysis session)**

- - Supply of 2nd dose study medication allopurinol 200mg/placebo x 3 dialysis sessions (+/- 1 dialysis session)
  - Record list of current medications
  - Vital signs
  - Assess any adverse events from visit 2 to visit 3a
  - Check drug compliance
  - Safety blood tests
- **Visit 3b Progress visit (Week 3 +/- 1 dialysis session)**
  - Supply of 3^rd^ dose study medication allopurinol 250mg/placebo x 3 dialysis sessions (+/- 1 dialysis session)
  - Record list of current medications
  - Vital signs
  - Safety bloods
  - Assess any adverse events from visit 3a to visit 3b
  - Check drug compliance
- **Visit 3c-Progress visit (Week 4 +/- 1 dialysis session)**
  - Supply of 4th dose study medication allopurinol 300mg/placebo x 3 dialysis sessions (+/- 1 dialysis session)
  - Record list of current medications
  - Vital signs
  - Safety bloods
  - Assess any adverse events from visit 3b to visit 3c
  - Check drug compliance
- **Visit 3d-Progress visit (Week 5 +/- 1 dialysis session)**
  - Supply of 5th dose study medication allopurinol 350mg/placebo x 3 dialysis sessions (+/- 1 dialysis session)
  - Record list of current medications
  - Vital signs
  - Safety bloods
  - Assess any adverse events from visit 3c to visit 3d
  - Check drug compliance
- **Visit 4- Progress visit (week 6 +/- 1 dialysis session)**
  - Dispense study medication allopurinol at optimum dose/placebo x 5 months
  - Record list of current medications
  - Vital signs
  - Safety bloods
  - Assess any adverse events from visit 3 to visit 4
  - Check drug compliance
- **Visit 5- Progress visit (Month 6 +/- 2 weeks)**
  - Dispense study medication allopurinol/placebo x 3 months
  - Record list of current medications
  - Vital signs
  - Safety bloods
  - Assess any adverse events from visit 4 to visit 5
  - Check drug compliance
- **Visit 6- Progress visit (Month 9 +/- 2 weeks)**
  - Dispense study medication allopurinol/placebo x 3 months
  - Record list of current medications
  - Safety bloods
  - Vital signs
  - Assess any adverse events from visit 5 to visit 6
  - Check drug compliance
  - FMD measurements
  - PWV measurements
- **Visit 7- Final visit (Month 12 +/- 2 weeks)**
  - Review urate and safety bloods
  - Record list of current medications
  - Safety bloods
  - Vital signs

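### Phase 1 Visit 6 titrates to 350mg and gives a 350mg stat dose, but its supply line dispenses 300mg

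*Protocol*

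**What the plan says.** Protocol section 7.1, Phase 1, Visit 6 (13th dialysis session) contains three dose lines. If the urate fall is still below 50%, the patient is to "titrate up to 350mg allopurinol". The next line is "Stat Dose 350mg Allopurinol". The one after that is "Supply of 5th dose study medication allopurinol 300mg x 3 dialysis sessions", with a tolerance of one session either way.

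The rest of the Protocol describes the top step differently from that third line:

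- The Experimental Design text for Phase 1 sets out the ladder after 200mg: "The next step will be 250mg and then 300mg and 350mg (maximum dose". Section 3 repeats the same steps.
- The Phase 1 flow chart in section 3 has patients without a sufficient fall "continue until 350mg allopurinol max dose".
- Section 6.1.1 lists a separate 350mg capsule.
- The Appendix 2 schedule puts 350mg in the Visit 6 column and stops dosing at Visit 7.
- The corresponding Phase 2 line, at Visit 3d in section 7.1, reads "Supply of 5th dose study medication allopurinol 350mg/placebo x 3 dialysis sessions".

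On how the readings are used, the Experimental Design text says of the first step: "Plasma urate will be checked at the commencement of the fourth dialysis session". The same procedure then applies at each higher dose. It goes on: "From these pilot data, we will calculate which of the above doses of allopurinol" gives an average urate fall of 41%, and that dose goes into the main trial.

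**The concern.** One visit prescribes one strength and dispenses another. This is an operative instruction to the person handing out capsules, not background text.

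The 350mg step has a single urate reading, at Visit 7, and no later visit could replace it. If 300mg capsules were issued, the value filed under 350mg would come from one 350mg dose followed by 300mg doses. Phase 1 exists to map each dose to its average urate fall, so a mislabelled top step would blur the comparison between 300mg and 350mg. Phase 1 has ten patients in all, and only those still below a 50% fall reach this step, so there may be few values to inform it.

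**Working it through.** **Step 1: is Visit 6 the odd one out?** Doses in section 7.1, Phase 1, against the Appendix 2 dose row:

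| Visit | Titrate to | Stat dose | Supply line | Appendix 2 |
|---|---|---|---|---|
| 3 | 200mg | 200mg | 200mg | 200mg |
| 4 | 250mg | 250mg | 250mg | 250mg |
| 5 | 300mg | 300mg | 300mg | 300mg |
| 6 | 350mg | 350mg | **300mg** | 350mg |

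Visit 2 supplies 100mg, as Appendix 2 shows. Visit 6 is the only mismatch, and its supply figure repeats that of Visit 5. A fifth dose equal to the fourth would not be an escalation step. A carry-over from the Visit 5 line is the likeliest explanation.

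**Step 2: dose received if the line were followed literally.** Inputs: Visit 6 at session 13 and Visit 7 at session 16 (section 7.1 and Appendix 2); dosing after each session, with urate read at the start of the later session (Experimental Design). Assumption: the stat dose is the session-13 dose. This fits the description of three doses per step.

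- Doses before the Visit 7 reading: n = 16 − 13 = 3
- Received: 350 + 2 × 300 = 950mg
- Intended: 3 × 350 = 1050mg
- Shortfall: (1050 − 950) / 1050 = 9.5%
- Share of the intended increment over the 300mg step: (950 − 900) / (1050 − 900) = 1/3

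**Step 3: sensitivity.** If the stat dose is additional to a session-13 dose from the supply, n = 4. Received is 350 + 3 × 300 = 1250mg against 4 × 350 = 1400mg, 10.7% less.

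Visits 6 and 7 each have a window of one session either way. With the stat dose counted as the Visit 6 dose, the extremes are:

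- Visit 6 at session 14, Visit 7 at session 15: n = 1, one 350mg dose, no shortfall.
- Visit 6 at session 12, Visit 7 at session 17: n = 5, 350 + 4 × 300 = 1550mg against 1750mg, 11.4% less. This needs the extra session of supply that the tolerance allows.

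On that counting the shortfall runs from 0% to 11.4% over all the windows, with 9.5% on the nominal schedule. These are dose figures. The Protocol gives no dose-response from which to convert them into a urate difference.

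**The case against.** The strongest reply is that the document resolves the matter itself. The two lines directly above the error say 350mg, section 7.1 opens by referring the reader to Appendix 2, and Appendix 2 shows 350mg at Visit 6. Staff would have to step down from the stat dose just given while calling the lower strength the fifth dose. That is possible but unlikely. The same visit list has another apparent carry-over: the Visit 7 adverse-event line names the interval between Visits 4 and 5. This reply stands, and it is why the point is minor. It does not make the line correct.

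The consequence is also conditional at each step. The wrong line must be followed, a patient must reach Visit 6 with less than a 50% fall, 350mg must be a serious candidate for the average 41% fall, and the value must be filed under the nominal dose. The Protocol does not say how many of the ten patients would get that far. Distinct capsule strengths (section 6.1.1) and accountability logs (section 6.1.7) should make a wrong issue traceable. All of this stands too.

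A reader might infer more: that Phase 1 was meant to stop at 300mg, that the Phase 2 dose would be wrongly chosen, or that patients are put at risk. The documents support none of these. Every other source names 350mg as the top step, there is no dose-response from which to derive a change in the chosen dose, and the error is towards a strength that the patient has already taken.

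**Conclusion.** The Visit 6 supply line is wrong as written and contradicts the rest of the Protocol. It is a minor internal inconsistency in one dispensing figure, and no design decision is at fault. If it were followed on the nominal schedule, with the stat dose counted as the session-13 dose, the sole reading for the 350mg step would follow only one third of the intended increase over 300mg and so would not measure that step. One of five dose levels is involved. The effect on urate and on the choice of Phase 2 dose cannot be sized from the document. The Phase 2 sample size and primary comparison are untouched.

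**What to change.** In section 7.1, Phase 1, Visit 6, change the supply line from 300mg to 350mg for 3 dialysis sessions, matching Appendix 2 and the Phase 2 Visit 3d line. If Phase 1 dosing has already taken place, check the accountability logs for patients who reached Visit 6. Where 300mg was issued, attribute that patient's Visit 7 urate to the doses actually given when the Phase 2 dose is calculated. The cost is one figure in the text and one look at the logs.

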**Phase 2 ALTERED Trial**

- **Visit 1 – Screening visit 1**
  - Participant consent– answer any outstanding questions and complete consent form.
  - Clinical Examination, Medical and Family history
  - Baseline Urate bloods
  - ECG
  - Safety bloods
  - Echocardiogram if not done in previous 2 years
  - MRI Scan –(***Only if Echo demonstrates LVH)***
  - 24hr BP monitoring
  - Record list of current medications
- **Visit 2 – Baseline visit (Day 0) upto 4 week post screening-**
  - Vital signs
  - Dosing with Allopurinol 100mg/placebo
  - Supply of 1^st^ dose study medication allopurinol 100mg x 6 dialysis sessions (+/- 1 dialysis session)
  - Record list of current medications
  - Assess any adverse events from screening visit to randomisation
  - Safety & research bloods
  - FMD & PWV measurements if participant agrees

**N*ote visits 3a- 3d are dependent on pilot data deciding eventual optimum dose of allopurinol***

**Visit 3a- Progress visit (Week 2 +/- 1 dialysis session)**

- - Supply of 2nd dose study medication allopurinol 200mg/placebo x 3 dialysis sessions (+/- 1 dialysis session)
  - Record list of current medications
  - Vital signs
  - Assess any adverse events from visit 2 to visit 3a
  - Check drug compliance
  - Safety blood tests
- **Visit 3b Progress visit (Week 3 +/- 1 dialysis session)**
  - Supply of 3^rd^ dose study medication allopurinol 250mg/placebo x 3 dialysis sessions (+/- 1 dialysis session)
  - Record list of current medications
  - Vital signs
  - Safety bloods
  - Assess any adverse events from visit 3a to visit 3b
  - Check drug compliance
- **Visit 3c-Progress visit (Week 4 +/- 1 dialysis session)**
  - Supply of 4th dose study medication allopurinol 300mg/placebo x 3 dialysis sessions (+/- 1 dialysis session)
  - Record list of current medications
  - Vital signs
  - Safety bloods
  - Assess any adverse events from visit 3b to visit 3c
  - Check drug compliance
- **Visit 3d-Progress visit (Week 5 +/- 1 dialysis session)**
  - Supply of 5th dose study medication allopurinol 350mg/placebo x 3 dialysis sessions (+/- 1 dialysis session)
  - Record list of current medications
  - Vital signs
  - Safety bloods
  - Assess any adverse events from visit 3c to visit 3d
  - Check drug compliance
- **Visit 4- Progress visit (week 6 +/- 1 dialysis session)**
  - Dispense study medication allopurinol at optimum dose/placebo x 5 months
  - Record list of current medications
  - Vital signs
  - Safety bloods
  - Assess any adverse events from visit 3 to visit 4
  - Check drug compliance
- **Visit 5- Progress visit (Month 6 +/- 2 weeks)**
  - Dispense study medication allopurinol/placebo x 3 months
  - Record list of current medications
  - Vital signs
  - Safety bloods
  - Assess any adverse events from visit 4 to visit 5
  - Check drug compliance
- **Visit 6- Progress visit (Month 9 +/- 2 weeks)**
  - Dispense study medication allopurinol/placebo x 3 months
  - Record list of current medications
  - Safety bloods
  - Vital signs
  - Assess any adverse events from visit 5 to visit 6
  - Check drug compliance
  - FMD measurements
  - PWV measurements
- **Visit 7- Final visit (Month 12 +/- 2 weeks)**
  - Review urate and safety bloods
  - Record list of current medications
  - Safety bloods
  - Vital signs
  - Assess any adverse events from visit 5 to visit 6
  - Check drug compliance
  - FMD measurements
  - PWV measurements
  - ECG
  - MRI Scan – may be done upto 2 week post visit

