**Phase 2: Main ALTERED Trial**

The main trial will be a 12 month, placebo-controlled, randomised, double-blind, parallel-group study. After baseline assessments and investigations, patients will be then randomly assigned to receive an allopurinol capsule (100mg, start dose then increased to maximum dose decided from the dose ranging preliminary phase of the trial) or placebo capsule for 2 weeks of dialysis sessions (typically 6 dialysis sessions).

Randomisation will be done by Tayside Pharmaceuticals and will be stratified by site to ensure balance. Each dose will be given at the end of each dialysis session.

If this 100mg start dose is tolerated, this would be increased at weekly intervals to the allopurinol dose chosen by the pilot study. Baseline blood samples will be taken for full blood count, renal function, liver function, random blood glucose, haemoglobin A1C, lipids, calcium and phosphate, and these would be repeated at 6, 9 and 12 months. However, urate levels will be stored and measured at the end of the study in order to ensure blinding throughout. Subjects will be followed at baseline, week 2, week 6, month 5, month 9 and 12 with close monitoring of their full blood count and renal function. Office BP will be measured thrice at each visit and the average of the second and third reading will be recorded and also pre and post dialysis. BP is recorded as part of standard care and will be available for analysis. 24 hour BP will also be measured at baseline and at 12 months.

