**Enrolment**

The Phase 1 dose escalation study is an open label study undertaken to see which dose of active allopurinol reduces plasma urate by the same margin (41%) as seen in our previous CKD stage 3 study where allopurinol did regress LVH.[[21](#_ENREF_21)]

Ten patients with CKD stage 5 will initially receive 100 mg allopurinol daily after each dialysis session for a total of 3 dialysis sessions. Plasma urate will be checked at the commencement of the fourth dialysis session. Thereafter the allopurinol dose will be increased to 200mg and the same procedure repeated. The next step will be 250mg and then 300mg and 350mg (max).

The dose escalation will **stop** in each patient when plasma urate has fallen by >50% in that patient which is in keeping with published recommendations to ensure safe prescribing of allopurinol in ESRD. [[28](#_ENREF_28)]

From these pilot data, we will calculate which of the above doses of allopurinol (given at the end of each dialysis session) produces on average a 41% fall in plasma urate. This will be the chosen dose for the ALTERED trial.

There will be a pause between the two phases of the study to calculate the optimum dose and prepare IMPs required for the main phase 2 trial.

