If study drugs are tolerated, the dose would be increased at weekly intervals after the 200mg dose to the allopurinol dose chosen by the dose escalation study, if greater than 200mg. Baseline blood samples will be taken for full blood count, renal function, liver function, random blood glucose, haemoglobin A1C, lipids, calcium and phosphate, and these will be repeated at 6, 9 and 12 months, bar lipids which are tested at baseline and final visit only. However, urate levels will be stored and measured at the end of the study in order to ensure blinding throughout. Subjects will be followed at baseline, week 2, week 6, month 6, month 9 and 12 with close monitoring of their full blood count and renal function. Research bloods for BNP measurement and inflammatory markers will be taken at baseline, and at months 6, 9 and the final 12 month study visit. Office BP will be measured thrice at each visit and the average of the second and third reading will be recorded. Furthermore pre and post dialysis. BP is recorded as part of standard care and will be available for analysis. 24 hour BP will also be measured at baseline and at 12 months.

Patients will continue with all their usual medication, which will remain unchanged throughout unless clinically indicated.

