**FMD**

FMD will be offered to all participants in the main trial, but may be declined without affecting their participation in the main trial.

FMD on the brachial artery will be performed in the non-fistula arm on three visits (baseline, month 9 and month 12) using a Philips iE33 ultrasound machine (Phillips Medical Systems, United Kingdom) according to the guide-lines set by the International Brachial Artery Reactivity Task Force.[[33](#_ENREF_33)] The brachial artery will be longitudinally imaged above the elbow using an 11.3-MHz probe. The image will be recorded for 2 minutes, followed by induction of forearm ischaemia by inflating a cuff below the elbow to 200 mmHg (or 50 mmHg above SBP, whichever is higher) for 5 minutes and deflating rapidly. The resulting reactive hyperaemia will be recorded for a further 2 minutes. After a rest period of 10 minutes, the procedure will be repeated, with 0.4mg of glyceryl trinitrate being administered sublingually to determine endothelium-independent dilation. FMD will be expressed as per cent change in diameter relative to the baseline diameter at rest. Analysis of all FMDs will be performed on the Brachial Analyser version 5.0 software (Medical Imaging Applications, LLC) by a single trained investigator (the clinical research fellow) to avoid inter-observer variability. This investigator will be blind to allocated treatments. Our intra-observer coefficient of variation for FMD is usually 5.2%. Two factors should ensure reliable results despite there being two sites : each patient will always be studied on the same equipment and the same individual (the research fellow) will do all the tests and interpret them (blindly) at both sites. For further reassurance, blinded ultrasound scans will be re-analysed to ensure good reproducibility at each site and between sites.

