## END OF STUDY

The end of study is defined as the last participant last visit (LPLV)

The CI and/or the TSC have the right at any time to terminate the study for clinical or administrative reasons.

The end of the study will be reported to the Sponsor, REC and Regulatory Authority within 90 days, or 15 days if the study is terminated prematurely. The CI will ensure that any appropriate follow up is arranged for all participants.

A summary report of the study will be provided to the Sponsor, REC and Regulatory Authority within 1 year of the end of the study.

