**PARTICIPANT STUDY SCHEDULE**

| CLINIC VISIT | **Visit**  **1**  **Screening** | **Visit 2**  **Baseline**  **Dialysis** | **Visit 3**  **(+/- 1 dialysis session)** | **Visit 4**  **(+/- 1 dialysis session)** | **Visit 5**  **(+/- 1 dialysis session)** | **Visit 6**  **(+/- 1 dialysis session)** | **Visit 7**  **Final Visit**  **(+/- 1 dialysis session)** |
| --- | --- | --- | --- | --- | --- | --- | --- |
|  | -1 to -4 weeks | **Day 0** | **4^th^ dialysis Session** | **7^th^ Dialysis session** | **10^th^ Dialysis Session** | **13^th^ Dialysis** | **16^th^ dialysis session** |
| Drug dose |  | 100mg | 200mg | 250mg | 300mg | 350mg | **Stop!** |
| Informed Consent | X |  |  |  |  |  |  |
| Check Inc/Exc Criteria | X |  |  |  |  |  |  |
| Medical History | X |  |  |  |  |  |  |
| Family History | X |  |  |  |  |  |  |
| Clinical Examination | X |  |  |  |  |  |  |
| Demographics | X |  |  |  |  |  |  |
| Vital Signs | X | X | X | X | X | X | X |
| **Urate** | X |  | X | X | X | X | X |
| Safety Blood Tests^A^ | X | X | X | X | X | X | X |
| Dispense Study medication |  | X | X | X | X | X |  |
| Adverse Event Assessment |  | X | X | X | X | X | X |
| Record or Review Con Meds | X | X | X | X | X | X | X |
| Check Drug Compliance |  |  | X | X | X | X | X |

**A: Safety blood tests**: U&Es, LFT’s, FBC, HbA1C, glucose, Calcium, Phosphate

Note that Urate result must be reviewed prior to dispensing of any medication. If urate has decreased by >50% since screening then participant is finished in trial and does not need to continue with higher dose medication.

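### Phase 2 Visit 7 tells staff to review urate at month 12, contradicting the rule that urate stays unmeasured until the end of the study to protect the blind

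*Protocol*

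**What the plan says.** **The blinding rule.** Both descriptions of the main trial, in Experimental Design and in section 3, state it. The section 3 text reads: "urate levels will be stored and measured at the end of the study in order to ensure blinding throughout". Section 14.4 defines the end of study for the whole trial, as the last participant's last visit.

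**The visit list.** Section 7.1, Phase 2 Visit 7 (month 12), opens with "Review urate and safety bloods". Safety bloods then appear again as a separate item, followed by FMD, PWV, ECG and the MRI scan, which "may be done upto 2 week post visit". The Phase 2 screening visit in the same section includes baseline urate bloods.

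**The schedule table.** Appendix 3 groups urate with the research bloods at baseline, week 6 and months 6, 9 and 12. It shows no urate at screening and no review step.

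**Who assesses outcomes.**
- FMD is analysed "by a single trained investigator (the clinical research fellow) to avoid inter-observer variability". The FMD text says the same person does all the tests and must be blind.
- The Applanation Tonometry text has the research fellow, also blind, perform PWA and PWV at both sites.
- The CMRI Methods text has LV mass read offline by one blinded observer for both sites.
- Section 8.1 names the research fellow as one of two roles collecting the data.

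**The concern.** The protocol treats urate as a marker of allocation and withholds it for that reason. The Phase 2 dose is the one that "produces on average a 41% fall in plasma urate" in Phase 1, so a seen on-treatment value, set against a pre-treatment one, points towards the arm.

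The month 12 visit is where the final FMD and PWA/PWV are done, and the person doing them may also be running the visit. Both methods depend on the operator, and FMD also on the reader. If that person has seen the urate result, the assessor blinding the protocol requires is lost for those measurements. Adverse events assessed at or after that visit are exposed in the same way, though less so. Sites work from the visit list, so a drafting slip there can turn into practice.

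**Working it through.** The plan states no figure on this point, so the main check sets the texts side by side.

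**1. Can both instructions be followed?** A sample that is stored and unmeasured has no result to review. They could be reconciled only by one of two readings:

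- *The end of the study means each participant's own month 12.* Section 14.4 rules this out. Section 4.1 plans one year of recruitment, and treatment lasts 12 months. The first participant reaches Visit 7 at about month 12 of the trial and the last at about 12 + 12 = month 24, so early completers would have urate reviewed up to about a year before the end of the study.
- *Review means draw a sample.* Visit 7 lists safety bloods separately from the review item. In Phase 1, where the same review line appears, the note to the schedule says "Note that Urate result must be reviewed prior to dispensing of any medication", so the word there means looking at a result.

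Neither reading works. The contradiction is in current text and within the blinded phase.

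**2. Where does the line come from?** It is identical to the first item of the open-label Phase 1 Visit 7. The Phase 2 Visit 7 list shows other signs of copying: its adverse-event interval runs from visit 5 to visit 6, which is the interval of the preceding visit. Carry-over is the likely explanation.

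**3. Who could be unblinded, and for what?**
- *FMD and PWA/PWV*: directly exposed, because one named role performs them, reads FMD, and may collect the visit data.
- *Adverse events*: exposed only for events judged at or after Visit 7.
- *LV mass*: exposed only if the urate result reaches the blinded offline reader. Nothing in the protocol sends it there.

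**4. How informative would urate be? (Illustration only.)** Assumptions, none given by the protocol for Phase 2 at month 12: a mean fall of 41% on allopurinol, 0% on placebo, normally distributed change with the same SD in both arms, equal allocation, a known pre-treatment value, and a cut-off halfway between the arms.

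P(correct guess) = Φ((41/2)/SD) = Φ(20.5/SD)

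| SD (percentage points) | 20.5/SD | P(correct) |
|---|---|---|
| 10 | 2.05 | 0.98 |
| 15 | 1.37 | 0.91 |
| 20 | 1.03 | 0.85 |
| 25 | 0.82 | 0.79 |
| 30 | 0.68 | 0.75 |

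Chance alone gives 0.50. The formula concerns the *change* in urate, so it needs two measured values. The baseline sample in Appendix 3 falls under the storage rule. The screening sample in section 7.1 is not said to be stored, and it is the more likely route to a known starting value.

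**5. Does the present end-of-study definition fully protect the last participant?** Not quite. The final MRI may come up to 2 weeks after Visit 7. If last visit means Visit 7, urate could be assayed before the last scan is done or read.

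**The case against.** The strongest reply is that this is a stray line. The rule and its purpose are stated twice, no earlier Phase 2 visit reviews urate, and the schedule table lists only sampling, which is compatible with storage. That is fair. It makes this an internal contradiction rather than a deliberate design decision, but it does not make the visit list correct.

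The second reply is that harm is conditional. The month 12 sample is drawn at Visit 7, and neither the assay turnaround nor the order of procedures within the visit is stated. If FMD and PWA/PWV are finished before any result returns, they are unaffected. This stands, and the consequence has to be worded conditionally.

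The third reply is that other safeguards exist. FMD and PWA/PWV are optional secondary measures whose operator must be blind, and blinded ultrasound scans are to be re-analysed. Section 10.4 evaluates events as though the participant were on active drug, and section 10.4.2 says the blind is not broken for causality. These reduce the risk without removing it, because the operator's blindness is exactly what the Visit 7 line could undo.

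A reader might infer that blinding fails for the primary outcome. The documents do not support that, given the single blinded offline reader. A reader might also infer that one urate value identifies the arm almost with certainty. That is not supported either: the calculation needs a known starting value, an assumed SD and an assumed null placebo change. Participants taken off drug but kept in the study would lower the accuracy further.

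**Conclusion.** The Visit 7 line is wrong as written and must be reconciled with the storage rule. Confidence in the contradiction is high, and it rests on no assumption.

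The consequence is conditional and narrower. If the line is followed and a result is available in time, the research fellow could be unblinded, with the risk falling mainly on the month 12 FMD and PWA/PWV and on late adverse-event assessment. LV mass is largely protected unless the result reaches its reader. The illustrative range of about 75% to 98% correct guesses shows that a urate change would be informative over a wide span of SDs. It is not an estimate for this trial.

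**What to change.** - In section 7.1, Phase 2 Visit 7, replace the review line with: *Collect and store urate sample; review safety bloods only.*
- State that stored urate is assayed and released only after the last participant's MRI, FMD and PWA/PWV readings are locked. Tying release to locked readings rather than to the last visit covers an MRI done up to 2 weeks later.
- Reconcile the baseline urate item at the Phase 2 screening visit in section 7.1 with Appendix 3, which shows none, and with the storage rule. Either remove the item or say that this sample is also stored unmeasured.

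The cost is a few lines of text. Stored samples are already planned, so no extra visit, sample or assay is needed. An outcome assessed unblinded could not be corrected afterwards.
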